### Sample size calculation

The sample size for this study was determined based on previous related interventional trials with people with PD. The sample size was determined considering a two-sided alpha level and was based on a difference between two independent group means (*T*-Student’s test). Considering a 0.7 effect size (e.g., for the FES-I outcome), for 80% power and an alpha level of 5%, a sample size of 26 subjects per group will be required. With a dropout rate set at 15%, a final sample of 60 (*n* = 30 per group) was considered optimal. So, we will include 60 people with PD living in Portugal.

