### Randomization and blinding

After baseline assessments (T0), participants will be divided into two groups (one experimental group with trampoline training [EG] and one control group [CG]). Online software will be used to generate the randomization plan using a random block sizes method. This randomization procedure assures an allocation concealment format—i.e., the individual in charge of this task does not know what the next group allocation will be. This researcher will assign participants to their groups and perform follow-up measurements (Fig. 1). The data analysts will be blind to the group control or intervention.

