**Fig. 2 Fig2:**
[figure not shown]
Lisbon Intensive Falls Trampoline Training (LIFTT) Program weekly progression

Additionally, safe fall landing strategies will be taught and reinforced throughout the program but specifically trained in the last two weeks. There is emerging evidence to suggest that these landing strategies can be safe and effective for a geriatric population [30]; however, this intervention has not been examined in a clinical physical therapy practice setting in PD. This will be an additional novelty of our program.

At the end of each session, the therapist will document in the study log any adverse event, patient feedback about the exercises and need for support, motives for absence, and any reported falls that occurred during the training.

To ensure participant retention, we facilitate traveling with reimbursement of costs and a list of concierge services to choose from. The team applying the intervention will be asked to express appreciation weekly, do follow-up calls when someone is absent, and share weekly results reached.

In the control group, participants will continue to receive their usual care from the health services and only receive the assessments. The intervention group will go back to usual care during follow-up.

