### Data collection

Assessments will take place at APDPk by a blinded researcher in the week before (T0), after 8 weeks of training protocol (T1), and 3 months after the end of the program (T2). The same protocol will be applied, composed of scales/questionnaires and validated assessment instruments, referenced below. The researchers who will perform these assessments will not participate in the intervention. All participants will be assessed in the ON medication phase with the following specific clinical scales and tests that will have their order randomized. Patients will be assessed for (a) balance (Mini-BEST Test) [12], (b) gait (Motor and Cognitive Timed Up Go (TUG)) [12], (c) clinical impairments (Movement Disorder Society Unified Parkinson Disease Rating Scale (MDS-UPDRS)) [31], (d) frequency and severity of falls (falls weekly registry) [12], (e) fear of falling (Falls Efficacy Scale (FES-I)) [32], (f) physical capacity (6-min walking distance test (6MWD)) [12], (g) cognition (Montreal Cognitive Assessment (MoCA)) [33], and (h) quality of life (PDQ-8) [34, 35]. Additional gait and balance assessments will be conducted using accelerometers placed on the ankles and standing on a force plate. Participants will be asked to walk on a treadmill for 10 min at their preferred walking speed. Moreover, their balance will be tested in both eyes opened and closed conditions. They will be asked to remain still for 2 min. Researchers that will conduct the assessments will be trained by a senior and experienced researcher. The database obtained will undergo a double check (two different researchers) to identify potential failures/errors.

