### Data analysis

We will perform descriptive and inferential statistics of data collected at T0, T1, and T2, to identify the differences between the two groups (EG and CG) and to evaluate which of these groups will have better results as a function of time (from T0 to T1 and T2). Assessment of reliability and correlation analyses will also be conducted. We do not anticipate the possibility of performing subgroup analysis for this study. The protocol will not change during the entire interventional period of the study; therefore, no interim analysis will be performed, nor do we anticipate the need for stopping guidelines.

For achieving the objective mentioned above, we will use a factorial (two-way) repeated measures (RM) ANOVA, considering a between-subject factor (treatment: EG, CG) and a repeated measures factor (time: T0, T1, T2). The two-way RM ANOVA will allow to evaluate the individual contribution of each factor and their interaction throughout time. The latent growth modeling (LMG) technique will be conducted to establish the effectiveness of the individual intervention on the growth of primary outcomes during the period between the beginning (T0) and the end (T2) of the program.

Regardless of the potential dropouts missing data, we will include all the participants in the statistical analysis (i.e., intention-to-treat analysis).

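### The repeated measures ANOVA treats the pre-randomisation value (T0) as an outcome level and names no efficacy term; its treatment main effect is diluted by one third, and no baseline-adjusted contrast is described

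*Protocol article*

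**What the plan says.** The Data analysis section of the protocol article specifies a two-way repeated measures ANOVA, "considering a between-subject factor (treatment: EG, CG) and a repeated measures factor (time: T0, T1, T2"). It adds: "The two-way RM ANOVA will allow to evaluate the individual contribution of each factor and their interaction throughout time". The general aim given just before is "to evaluate which of these groups will have better results as a function of time (from T0 to T1 and T2"). None of the three terms (treatment, time, treatment by time) is designated as the test of efficacy.

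The Randomization and blinding section fixes the order of events: "After baseline assessments (T0), participants will be divided into two groups". T0 is therefore a pre-randomisation measurement.

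A second model, latent growth modelling, is planned "on the growth of primary outcomes during the period between the beginning (T0) and the end (T2) of the program". Data collection defines the later visits differently, as "after 8 weeks of training protocol (T1), and 3 months after the end of the program (T2"), so T2 is a follow-up visit rather than the end of training. Between T1 and T2 the Interventions section says: "The intervention group will go back to usual care during follow-up".

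No analysis is described in which the T0 value serves as a covariate, and neither T1 nor T2 is named as the primary visit.

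**The concern.** A value taken before randomisation cannot carry a treatment effect, so the expected EG–CG difference at T0 is zero. If T0 is one of three outcome levels, the treatment main effect is the average of that zero and the effects at T1 and T2. A reader who takes this term as the effect of training sees an estimate that is too small and a test with little power. The protocol invites that reading, because it says the contribution of each factor will be evaluated.

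The interaction avoids the dilution. But its F test has two degrees of freedom, and a significant result does not say at which visit or in which direction the groups differ. For a superiority trial, the quantity wanted is a group difference at a stated visit with a confidence interval. The T0 value that would sharpen this estimate is collected on every participant but is not described as being used for adjustment.

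**Working it through.** **Inputs from the protocol.** Sample size calculation: effect size 0.7, 80% power, alpha 5%, t-test on two independent means, 26 per group, 15% dropout, 60 in total (30 per arm). The alpha is two-sided: "The sample size was determined considering a two-sided alpha level". 30 × 0.85 = 25.5, so 26 per arm is a fair figure for those analysed.

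**Assumptions, not in the protocol.** SD 1 at each visit; equal correlation ρ between visits, 0.3 to 0.8; the 0.7 SD effect placed at T1; T2 effect 0.7 (kept), 0.35 (half kept) or 0 (lost).

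**Step 1: the plan's own figure.** n = 2(z_α + z_β)²/d². Two-sided: 2(1.960 + 0.842)²/0.49 = 32.04, hence 33 per group (exact t-test 33.02). One-sided: 2(1.645 + 0.842)²/0.49 = 25.2, hence 26. The stated 26 is reproduced only one-sided. With 26 per arm the two-sided t-test has 70% power. That is a separate sample-size matter; it is used here only as the reference for the unadjusted comparison.

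**Step 2: dilution of the main effect.** It estimates (0 + δ1 + δ2)/3, while the post-baseline average is (δ1 + δ2)/2. The ratio is always 2/3.
- Kept: 1.40/3 = 0.47, against 0.70.
- Half kept: 1.05/3 = 0.35, against 0.525.
- Lost: 0.70/3 = 0.23, against 0.35.

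**Step 3: power, n = 26 per arm, two-sided 5%, noncentral F.**
- Main effect: λ = (n/2)·δ̄²/[(1 + 2ρ)/3], df 1 and 50.
- Interaction: λ = (n/2)·Σ(δj − δ̄)²/(1 − ρ), df 2 and 100.
- ANCOVA at T1 with T0 as covariate: λ = (n/2)·δ1²/(1 − ρ²), df 1 and 49.

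Example, ρ = 0.5, half kept. Main effect: 13 × 0.1225/0.6667 = 2.39, power 32.9%. Interaction: 13 × 0.245/0.5 = 6.37, power 59.8%. ANCOVA: 13 × 0.49/0.75 = 8.49, power 81.5%.

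| ρ | Main effect, % (T2 kept / half / lost) | Interaction, % (kept / half / lost) | ANCOVA at T1, % |
|---|---|---|---|
| 0.3 | 61.8 / 39.6 / 20.4 | 57.5 / 45.3 / 57.5 | 73.7 |
| 0.5 | 52.4 / 32.9 / 17.3 | 73.1 / 59.8 / 73.1 | 81.5 |
| 0.6 | 48.7 / 30.4 / 16.1 | 82.7 / 70.1 / 82.7 | 87.1 |
| 0.7 | 45.4 / 28.3 / 15.2 | 92.3 / 82.7 / 92.3 | 93.4 |
| 0.8 | 42.6 / 26.5 / 14.4 | 98.7 / 95.0 / 98.7 | 98.5 |

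Allowing for chance imbalance in the covariate lowers the ANCOVA column by at most about 1 point (72.8, 80.7, 86.5, 92.9, 98.3). Simulation at ρ = 0.5 and 0.7 (8,000 trials per case) agrees with the formulas within about 1 point.

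**Step 4: gap between interaction and ANCOVA at T1.** Kept or lost: 16, 8, 4, 1 and 0 points for ρ = 0.3, 0.5, 0.6, 0.7 and 0.8. Half kept: 28, 22, 17, 11 and 3 to 4 points.

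**Step 5: a pattern that reverses the ranking.** With 0.35 SD at T1 and 0.7 SD at T2, ρ = 0.6: ANCOVA at T1 has λ = 13 × 0.1225/0.64 = 2.49 and power 34%; the interaction has λ = 13 × 0.245/0.4 = 7.96 and power 70%.

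**The case against.** The strongest reply is that the stated aim, comparing the groups' course from T0 to T1 and T2, is the interaction. There T0 is the reference for differential change, nothing is diluted, and the test is valid. This stands. A reader might infer that the whole analysis is diluted, or that the efficacy test has only 14 to 62% power; the document does not support that, because it never designates the main effect as the efficacy test. What remains is that it also plans to evaluate that term and does not exclude it from the role.

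Second, the advantage of adjustment depends on two unknowns, the correlation and the persistence of effect. This stands too: at ρ = 0.8 with the effect fully kept or lost there is no gain over the interaction. A reader might also infer that adjustment simply repairs the shortfall in power at 26 per group. At ρ = 0.3 it does not.

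Third, a reader might infer that T1 must be the primary visit. The protocol names no primary visit, follow-up is part of the design, and step 5 shows that the ranking follows the assumed effect pattern. An effect larger at T2 is not the obvious expectation once EG returns to usual care, but the choice of visit is the sponsor's.

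Fourth, follow-up contrasts and confidence intervals are commonly left to an analysis plan, and the latent growth model may supply a direction and an estimate. Both points are fair, and the absence of such detail is not held against the article. But the article does fix T0 as an outcome level and does list the terms to be evaluated, and it does not present the growth model as a baseline-adjusted contrast at a stated visit.

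**Conclusion.** The point holds in a limited form. The treatment main effect over T0, T1 and T2 is diluted by one third relative to the post-baseline average; this follows from T0 preceding allocation and needs no assumption about correlation or persistence. The interaction is undiluted and valid, but it is an omnibus test without a single directional estimate. Its power is between 0 and about 28 points below T0-adjusted ANCOVA at T1, given 26 per arm, 0.7 SD at T1, equal correlations of 0.3 to 0.8, and a T2 effect that is kept, halved or lost. The document supplies neither the correlation nor the effects by visit. The fault is one of efficiency and of an unclear efficacy estimate, not of type I error in the planned ANOVA, and it does not settle which visit should be primary.

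**What to change.** State that the treatment main effect over T0–T2 will not be used as evidence of efficacy. Estimate the EG–CG difference, with 95% CI, from a longitudinal model with T1 and T2 as the only outcome levels, adjusted for the T0 value of the same outcome; a model with T0 constrained to be equal between arms serves equally well. Name one visit contrast as primary in advance and report the other from the same model as secondary. T1, the end of training, is a reasonable choice but the sponsor's to make.

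At 26 per arm and d = 0.7 at the chosen visit, the adjusted contrast has about 74% two-sided power at a baseline correlation of 0.3, 81% at 0.5, 87% at 0.6 and 93% at 0.7, against 70% for the unadjusted t-test. Any statement that 80% is reached should therefore carry the condition that the correlation is about 0.5 or more. The cost is analysis wording only: no new data and no added burden on participants.

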### Interventions

The intervention for the EG will consist of an 8-week individual training regime (1-h individual training, three times per week). Sessions will be led by a physiotherapist specializing in PD and motor and cognitive exercise programs. This health professional will ensure adaptation, specificity, progression, variation, and safety of the training. Guidance for exercise in PD was underpinned by clinical experience and evidence from the European Physiotherapy Guidelines for PD [20]. Each session will start with a 10-min warm-up outside of the trampolines, comprising a variety of whole-body amplitude-based movements and walking activities. It will end with a 10-min cooldown incorporating breathing and low amplitude movements as active stretching. The sessions will consist of performing motor exercises on the trampolines while adding in motor and cognitive exercises that will progressively be increased. Motor exercises will include an array of frequently recommended movements for PD that directly enhance specific functional activities of daily living, such as multidirectional stepping in place, sitting and standing, standing with good posture under unexpected balance challenges, reaching in diverse directions (e.g., catching a ball), carrying soft objects (while standing and walking), walking, turning and running, and getting up from the floor/trampoline [20]. All these physical exercises will focus on reinforcing the use of high-amplitude, multidirectional movements with increasing speed and complexity. Because people with PD often depend on cues when performing motor tasks during the sessions, cueing strategies (cognitive, visual, tactile, or verbal) will be used according to the patient’s needs to promote good-quality movement and reduce compensations [20, 27, 28]. Cognitive exercises will target the 4 main cognitive domains particularly affected by PD: attention, working memory, executive function, and visual exploration [29]. The dual cognitive tasks will include standing, sitting/standing, stepping, or walking while performing cognitive tasks such as simple talking, memorizing lists of words, alternating sentences, spelling words backward, counting a 7-digit number forward/backward, and quick decision-making.

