The intensity of the training plays an important role in expected outcomes [9, 37, 38]. Previous research showed that a high balance intensity dual-task walking program benefited balance and gait abilities in people with PD performed when applied in groups of four to seven participants, three times per week, 60 min per session, for 10 weeks at a university hospital [9]. Notably, later, a 6-week home program (one session per week with the therapist for six consecutive weeks and a weekly self-directed home program) that combined strength, movement strategy training, and falls education did not prevent falls in the long term due to insufficient dosage of therapy delivered [38].

Additionally, identifying effective outcome measures that are responsive to such interventions is also needed to improve the ability to design future clinical studies with such programs. The results will also contribute to the urgent knowledge needed to define clear dual motor-cognitive task recommendations for PD.

We expect one limitation to the proposed study regarding the lack of an active control group. In Portugal, there is no uniform standard physiotherapy treatment for people with PD. For this reason, this study will compare its results to the effect of physiotherapy treatment considered usual for each individual patient (no physiotherapy, falls education, exercise in the community, number of sessions of rehabilitation).

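### The latent growth model is to establish effectiveness over T0 to T2, called the end of the programme, but the programme ends at T1; a single T0-to-T2 slope, if fitted, would dilute an effect that fades

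*Protocol article*

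**What the plan says.** Four statements in the protocol article bear on this.

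- Interventions fixes the length of training: "The intervention for the EG will consist of an 8-week individual training regime".
- Data collection defines the visits. T0 is in the week before; the later two are "after 8 weeks of training protocol (T1), and 3 months after the end of the program (T2").
- The last paragraph of the Interventions text says what happens between T1 and T2: "The intervention group will go back to usual care during follow-up".
- Data analysis names two models. The first is a two-way repeated measures ANOVA with treatment as the between-subject factor and T0, T1 and T2 as levels of time. The second is a latent growth model, whose purpose is "to establish the effectiveness of the individual intervention on the growth of primary outcomes", over the span "during the period between the beginning (T0) and the end (T2) of the program".

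The article gives no functional form, loadings or time coding for the growth model.

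**The concern.** T2 cannot be both the end of the programme and three months after it. The slip sits in the sentence that says what the growth model estimates and that gives this model the task of establishing effectiveness. Read literally, the window joins 8 weeks of training to three months of usual care.

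If one growth rate is fitted across that window, it answers neither natural question cleanly. It is not the effect at the end of training and it is not the effect remaining at follow-up. Where benefit rises to T1 and then fades, one line through three points understates the gain at T1. The trial could then have two analyses of the same primary outcomes that disagree, with the less suitable one designated to establish effectiveness.

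**Working it through.** **Step 1. The text.** Training lasts 8 weeks (Interventions). T1 comes "after 8 weeks of training protocol (T1") and T2 "3 months after the end of the program (T2") (both Data collection). The programme therefore ends at T1. The span in Data analysis contradicts this, and no calculation is needed to show it.

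**Step 2. Inputs for the size of the consequence.**

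- From Sample size calculation: 26 per group, effect size d = 0.7, two-sided 5% level. The article gives no power figure for the growth model, so there is none to reproduce. The 26 is used here only as the number analysed; how it was derived is a separate matter.
- From Data collection: T1 at 8 weeks = 1.84 months; T2 at 1.84 + 3 = 4.84 months.
- Assumed, not in the documents: one linear slope; SD 1 at each visit; equal correlation ρ = 0.6 between visits (range 0.5 to 0.7); true group difference 0 at T0, d at T1 and r × d at T2, where r is the share retained; normal approximation.

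**Step 3. Slope without baseline adjustment.** The mean time is 2.227 and the sum of squared deviations is 11.937. The weights (t − 2.227)/11.937 on T0, T1 and T2 are −0.187, −0.032 and +0.219. The end-of-training visit has a small negative weight, and T2 drives the slope.

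- r = 1: slope 0.187d per month, so the line implies 0.187 × 1.84 = 0.34d at T1.
- r = 0.5: 0.077d per month, implying 0.14d at T1.
- r = 0: −0.032d per month.

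The SE of the slope difference is √[(2/26)(1 − 0.6)/11.937] = 0.0508. At r = 0.5, z = 0.077 × 0.7/0.0508 = 1.06, so power is 19%. At r = 1, z = 0.187 × 0.7/0.0508 = 2.57, so power is 73%.

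**Step 4. Slope with a common randomised baseline.** With the group difference fixed at 0 at T0 and V the correlation matrix, the slope weights are t′V⁻¹/(t′V⁻¹t) and the SE is √[(2/26)/(t′V⁻¹t)] = 0.0458. The slope is 0.207d at r = 1, 0.104d at r = 0.5 and 0.001d at r = 0. At r = 0.5, z = 0.104 × 0.7/0.0458 = 1.59, so power is 36%. At r = 1, z = 3.17, so power is 89%.

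**Step 5. Contrasts at T1.**

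- Change score: SE = √[(2/26) × 2(1 − 0.6)] = 0.248, z = 2.82, power 81%.
- Baseline-adjusted: SE = √[(2/26)(1 − 0.6²)] = 0.222, z = 3.15, power 88%.

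Neither depends on what happens after T1.

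**Step 6. Like-for-like comparison at ρ = 0.6.**

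| Share retained at T2 | Slope, unadjusted | T1 change score | Slope, common baseline | T1 adjusted |
|---|---|---|---|---|
| All | 73% | 81% | 89% | 88% |
| Half | 19% | 81% | 36% | 88% |

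At half retention with ρ = 0.5 the four figures are 16%, 71%, 35% and 83%; with ρ = 0.7 they are 23%, 90%, 38% and 94%. If visits are coded 0, 1, 2 instead of in real time, the unadjusted slope weights are −0.5, 0 and +0.5, so T1 drops out. Half-retention power is then 24% at ρ = 0.5 and 37% at ρ = 0.7.

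**The case against.** The strongest reply is that the straight line is an assumption of this review. A three-wave growth model can free a loading or use a piecewise mean, and an article may leave that to a fuller document. This stands: the power figures are conditional on a single slope. The mislabelled window does not depend on it.

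The second reply is that the T1 effect is already covered. The repeated measures ANOVA treats T0, T1 and T2 as separate levels, so a rise followed by a fall can be seen there. This also stands, and it confines the harm to the growth model.

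The third is that change from T0 to T2 is a legitimate durability question. It is, but the article describes the span as that of the programme and the aim as effectiveness.

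A reader might infer three stronger things.

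- *That the slope would reverse a real effect.* Under real-time coding, equal correlation and no baseline adjustment, the sign turns negative only if less than about 15% of the benefit remains at T2 (about 30% under a first-order autoregressive correlation of 0.7). Even at complete loss, the chance of a significant wrong-sign slope is about 6% to 7%. With a common baseline at ρ = 0.6, the slope at complete loss is essentially zero.
- *That a slope loses much power even when the benefit lasts.* Comparing an unadjusted slope (73%) with a baseline-adjusted T1 contrast (88%) suggests this, but it adjusts only one side. Like for like, the figures are 73% against 81%, and 89% against 88%.
- *That participants have no training between T1 and T2.* The article says usual care, and its Discussion lists what that may cover: "no physiotherapy, falls education, exercise in the community, number of sessions of rehabilitation".

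**Conclusion.** The point holds as a mislabelled effectiveness window with a conditional consequence. That the programme ends at T1 and not T2 is certain from the text. That a T0-to-T2 growth rate would dilute a fading effect follows only if one linear slope is fitted, which the article neither states nor excludes.

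Under that assumption the dilution is substantial when half the effect is lost: power of 19% against 81% unadjusted, or 36% against 88% adjusted. It is slight or absent when the effect persists. Actual retention is unknown. The documents do not support a claim that the trial will miss or reverse a true effect, because the ANOVA retains T1 as its own level. The text should be corrected before analysis.

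**What to change.** In Data analysis, state that T1 is the end of the programme and T2 the follow-up visit. Base the effectiveness conclusion on the baseline-adjusted group contrast at T1, and the durability conclusion on the contrast at T2.

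If the growth model is kept, call it exploratory, use actual visit times, and give it separate mean changes for T0-T1 and T1-T2. Its random slopes must be constrained. Three visits supply 6 variances and covariances, whereas a random intercept with two random slopes needs 6 and at least one residual variance makes 7. With three free means per group, the piecewise mean structure is saturated and reproduces the group-by-time contrasts already in the ANOVA, so it adds little as a test of effectiveness.

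The cost is a few sentences in the analysis section. No visit, measurement or participant is added.

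### The planned repeated-measures ANOVA, with no missing-data method stated, does not support the promise to include all participants

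*Protocol article*

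**What the plan says.** All of the analysis statements are in the Data analysis section of the protocol article.

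- **Group comparison:** "we will use a factorial (two-way) repeated measures (RM) ANOVA", with treatment as the between-subject factor and "a repeated measures factor (time: T0, T1, T2") as the within-subject factor.
- **Second model:** "The latent growth modeling (LMG) technique will be conducted". It is tied to the growth of the primary outcomes between T0 and T2. No estimator is given.
- **Analysis set:** "Regardless of the potential dropouts missing data, we will include all the participants in the statistical analysis (i.e., intention-to-treat analysis"). No imputation or likelihood method is named.

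Two other sections bear on the point. Sample size calculation states "a sample size of 26 subjects per group will be required" and then "With a dropout rate set at 15%, a final sample of 60", so incomplete follow-up is expected. Ethics and dissemination says that participants who stop the intervention stay in follow-up unless they withdraw consent.

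**The concern.** The section fixes both a method and an analysis set, and the two agree only if something unstated is added. A classical two-way repeated-measures ANOVA works on participants with a value at each level of the time factor. Someone assessed at T0 and T1 but not at T2 is removed for that outcome, and the T1 value goes too.

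Three things are at stake. First, the label: readers would take a completers' result for an analysis of everyone randomised. Second, information: T1 is the assessment immediately after the programme, and values observed there would be discarded because of a visit three months later. Third, possible bias: if the reasons for missing T2 relate to how participants are doing and differ between the arms, the completers no longer represent the randomised comparison.

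**Working it through.** **The plan's own figures.** Inputs from Sample size calculation: 26 per group, effect size 0.7, two-sided 5%, 80% power, 15% dropout, 60 in total.

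- 26 × 1.15 = 29.9, which rounds up to 30 per group and 60 in total. Dividing instead gives 26 / 0.85 = 30.6, so 31 per group and 62 in total.
- The 26 itself does not reproduce for a two-sided 5% test, which needs 33 (normal approximation) or 34 (exact t). It matches a one-sided 5% test (power 80.1%). That is a separate matter and is not used below.

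**How many would be analysed.** Assume that the whole dropout allowance turns into at least one missing visit and that nothing is imputed.

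- Analysed = 60 × (1 − 0.15) = 51; left out = 9.
- Range: at 5% dropout, 60 × 0.95 = 57; at 25%, 60 × 0.75 = 45.

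**Power.** The yardstick is the two-sample t-test on which the plan was sized, at d = 0.7 and two-sided 5%. The noncentrality is d × √(n₁n₂ / (n₁ + n₂)), with n₁ + n₂ − 2 degrees of freedom.

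| Analysed | n₁, n₂ | Noncentrality | Power |
|---|---|---|---|
| 60 | 30, 30 | 0.7 × √15 = 2.71 | 76.0% |
| 57 | 28, 29 | 2.64 | 73.8% |
| 51 | 25, 26 | 2.50 | 68.8% |
| 45 | 22, 23 | 2.35 | 63.1% |

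The 60-participant row is the ceiling with complete data. A likelihood analysis recovers the observed values that deletion throws away, but not the values that were never measured.

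**Bias.** The documents give no dropout by arm and no reasons for it, so every input here is an assumption: true group differences of 0, 0.70 and 0.35 SD at T0, T1 and T2; correlation 0.6 between any two visits; large samples. In the intervention arm (EG), the logit of missing T2 is −1.9 − 1.2 × (T1 residual), so those doing poorly at T1 are more likely to be missing. In the control arm (CG) it is −1.9 for everyone. This gives about 18% missing in EG and 13% in CG.

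| Group difference (SD) | T0 | T1 | T2 |
|---|---|---|---|
| True | 0 | 0.70 | 0.35 |
| Completers, raw | 0.11 | 0.88 | 0.46 |
| Completers, change from T0 | – | 0.77 | 0.35 |
| All observed data, likelihood, change from T0 | – | 0.70 | 0.35 |

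The treatment-by-time term measures change, so the third row is the relevant one: 0.88 − 0.11 = 0.77 at T1 and 0.46 − 0.11 = 0.35 at T2. The bias is 0.77 − 0.70 = 0.07 SD at T1 and nil at T2.

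For scale, the standard error of the T1 change contrast with 25 and 26 completers is √(2 × (1 − 0.6) × (1/25 + 1/26)) = 0.25 SD. The bias is about 0.07 / 0.25 = 0.28 of a standard error.

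With the EG dropout rule applied to both arms, the completers' changes are 0.70 and 0.35: no bias at either visit.

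**The case against.** Four points can be made for the plan.

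- **Imputation may be specified elsewhere.** A repeated-measures ANOVA on multiply imputed data includes everyone, and a full protocol or SAP could say so. This stands. A reader might infer that the ANOVA can never deliver the promised analysis; the documents do not support that. What remains is that the article commits to a method and to a set of participants, and names nothing that joins them.
- **A second model is named.** A latent growth model fitted by full-information maximum likelihood keeps incomplete participants. A reader might infer that the missing participants vanish from every test; that overlooks this model. But its estimator is not stated and it is confined to the primary outcomes. Fear of falling, falls, walking distance, cognition and the clinical rating scale are left to the ANOVA.
- **Follow-up continues after training stops.** With this provision and the retention measures under Interventions, leaving the programme does not by itself create a missing visit. The loss may therefore be smaller than 9, and the case for loss that differs by arm is weaker. Withdrawn consent and missed visits remain, and deletion works outcome by outcome.
- **The bias is modest and conditional.** A reader might take the raw completers' T1 difference of 0.88 SD as the distortion of a true 0.70. That is the wrong contrast: it carries a 0.11 SD baseline gap that the change scale removes. The 0.07 SD that is left needs a one-arm dropout mechanism which the documents neither state nor rule out.

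**Conclusion.** The point holds as a conflict within the Data analysis section, on the condition that no imputation is used. As written, the ANOVA would be a completers' analysis carrying an intention-to-treat label, and it would discard T1 values already collected.

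At the planned 15% dropout, about 51 of 60 participants would be analysed, and t-test power at d = 0.7 would be 68.8% rather than 76.0%. Both figures assume that all dropout becomes missing visits, so they mark the planning case and are not a forecast.

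Material bias is not established. It is about 0.07 SD in the T1 change under the assumed one-arm mechanism, nil in the T2 change, and nil when both arms share the dropout rule. The documents do not support a claim of a large or certain bias, or a claim that no analysis in the plan could retain incomplete participants.

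**What to change.** 1. Replace the ANOVA with a likelihood-based linear mixed model on all observed T1 and T2 values, with treatment, time, treatment-by-time and baseline, and with each randomised participant in the assigned group. REML with an unstructured covariance and Kenward-Roger degrees of freedom is one suitable specification. Running the ANOVA on multiply imputed data would also reconcile the two statements.
2. State that the latent growth model for the primary outcomes is fitted by full-information maximum likelihood.
3. Add one sensitivity analysis for missing data, such as a delta-adjusted multiple imputation. It can also take in anyone with a baseline value only, who contributes no follow-up value to the model in step 1.
4. Report the number contributing to each outcome at each visit, by arm.

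The cost is a change of analysis wording and slightly more analysis work. No further participants, visits or measurements are needed. The change should be made before the data are analysed.
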